**Methods/design:**

In this multicenter randomized controlled clinical trial, 290 patients newly diagnosed with neurosyphilis will be randomized 1:1 to treatment with aqueous crystalline penicillin G (ACPG) or ceftriaxone. Patients will be treated with standard regimens of ACPG or ceftriaxone according to Chinese National Guidelines and will be followed up for 12 months. All clinical parameters will be assessed at baseline and at follow-up 3, 6, 9, and 12 months later. The primary outcomes will include cerebrospinal fluid (CSF) white blood cell (WBC) count, serological efficacy, and clinical efficacy. The secondary outcomes will include CSF protein concentrations, Mini-Mental State Examination (MMSE) scores, imaging results, recurrence, and time to recovery from neurosyphilis. Adverse events will be monitored and recorded during the trial.

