### Sample size

Sample size will be calculated as described [24]. A useful approximate formula is:$$D={\left(1+R\right)}^2/{\left(1-R\right)}^2\times f\left(\upalpha, \upbeta \right)$$

where *R* is defined as the hazard ratio or risk ratio (RR) and *f*(*α*, *β*) = (*Z*_*β*_ + *Z*_*α*/2_)^2^ equals 7.85 for 80% power, with α = 0.05 and where *Z* is a standardized normal deviation. The RR has been reported to be 1.5 for serological cure (i.e., a two-dilution decrease in CSF-VDRL titer or reversion to nonreactivity) of neurosyphilis treated with ceftriaxone and ACPG [14]. This calculation showed that 196 primary events are required. A recent retrospective study reported that the rates of serological responses in patients treated with ACPG and ceftriaxone were 82% and 88%, respectively [12]. Based on an expected rate of successful treatment of 85%, 230 participants will be recruited. Because rates of loss to follow-up in such clinical trials have not been reported, the loss to follow-up rate in the present trial was set at no more than 20% [25] to ensure the quality of this trial. Thus, a total of 290 patients will be recruited, with 58 at each study center.

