### Statistical analysis

All statistical analyses will be performed using SPSS 21.0 statistical software by biostatisticians blinded to group assignment. Missing data for the primary outcome will be imputed using the multiple imputation method. Serum and CSF RPR titers will be analyzed after log_2_ conversion. Normally distributed continuous variables in the two groups will be compared by *t* tests, and categorical variables will be compared by the *χ*^2^ test or *Fisher’s *exact test, as appropriate. Nonparametric variables will be compared by rank sum tests. The correlation between serum and CSF RPR titers will be analyzed using Spearman’s rank correlation tests. Based on the assumption that there are no obvious correlations between primary outcomes and that it will be impossible to determine which outcome has greater weight, the weights of these primary outcomes will be evaluated using the “Experts Scores” algorithm, with “overall response” to treatment evaluated according to the total efficacy scores from these primary outcomes. The results of each primary outcome will also be evaluated separately. The non-inferiority margin will be set at 10 percentage points for the absolute difference between the two groups. If the standard for non-inferiority is reached, all primary and secondary outcomes will be tested for superiority (*P*<0.05). Non-inferiority will be considered reached if conclusions drawn from the intention-to-treat (ITT) population, consisting of all patients who met the inclusion criteria, were randomized, and started treatment, and the per-protocol population, consisting of all patients with good compliance and who followed the protocol to completion of the treatment regimen, are consistent. Univariate analyses will be performed to identify potential factors associated with the treatment outcome, with variables having a *P* value ≤0.10 in univariate analyses included in a multivariate logistic regression model. Odds ratios (ORs), adjusted ORs (aORs), and their 95% confidence intervals (CIs) will be calculated. A two-sided *P value* <0.05 will be considered statistically significant. Because the efficacy and safety of ceftriaxone and ACPG are clear and both are recommended by Chinese National Guidelines, this trial will not include interim analyses.

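### The 10-point non-inferiority margin is attached to no named outcome, and passing it opens unadjusted superiority tests on all 12 listed outcomes

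*Protocol article*

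**What the plan says.** Under Primary outcomes, the protocol article defines four: CSF-WBC count, CSF RPR response, serum RPR response and improvement of clinical manifestations. Under Secondary outcomes it has eight headings: MMSE score, CSF protein, imaging, adverse events, nonresponse, recurrence, time to recovery and withdrawal.

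The Statistical analysis section combines the primaries into an overall response using expert weights. Its stated ground is "Based on the assumption that there are no obvious correlations between primary outcomes". It adds: "The results of each primary outcome will also be evaluated separately". It then sets a margin of 10 percentage points on the absolute difference between arms, without saying which outcome that difference is measured on. Non-inferiority counts as reached when the ITT and per-protocol conclusions agree. After that, "all primary and secondary outcomes will be tested for superiority", each at P<0.05.

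The Sample size section works from serological cure only: "The RR has been reported to be 1.5 for serological cure".

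**The concern.** A non-inferiority claim needs an endpoint and a decision rule. Here five quantities could carry the 10-point test, and the text does not say whether one, some or all of them must meet it. Agreement between two analysis populations does not settle this, because it says nothing about endpoints. As written, the outcome that met the margin could be chosen after the results are known.

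The next step makes this worse. Moving from non-inferiority to superiority on the same endpoint costs no alpha. Here, success on an unnamed endpoint opens tests of every primary and secondary outcome, each at the full 5% level. The trial is meant to inform treatment guidelines, so a chance finding of superiority on one of many outcomes could be read as confirmatory.

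**Working it through.** **1. The plan's own figures.** The event formula uses a factor that "equals 7.85 for 80% power, with α = 0.05". With a risk ratio of 1.5:

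- Events: 7.85 × (1 + 1.5)² / (1 − 1.5)² = 7.85 × 25 = 196.25. This matches: "This calculation showed that 196 primary events are required".
- Participants: 196 / 0.85 = 230.6, stated as 230.
- With 20% loss: 230 / 0.80 = 287.5, so 288, which becomes 5 × 58 = 290.

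The arithmetic reproduces. It concerns one outcome, serological cure, and does not use the 10-point margin. It therefore gives no allowance for several endpoints.

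**2. Inputs for the error rates.** Superiority family: 4 + 8 = 12 outcomes, each at two-sided 0.05 (from the document). Non-inferiority: 4 primaries, or 5 with the composite, each at one-sided 0.025 (assumed, as the counterpart of a two-sided 5% level). Correlations of 0.3 to 0.7 are assumed; the document gives none.

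**3. Formula under independence:** 1 − (1 − α)^k.

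- Superiority, either direction: 1 − 0.95^12 = 46.0%.
- Superiority, favouring ceftriaxone only: 1 − 0.975^12 = 26.2%.
- Non-inferiority, any one of 4 suffices: 1 − 0.975^4 = 9.6%.
- Non-inferiority, any one of 5 suffices: 1 − 0.975^5 = 11.9%.

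**4. With correlation.** Equally correlated normal test statistics, 300,000 simulated trials per setting (the column for 0 is the formula above):

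| Chance of at least one false positive | 0 | 0.3 | 0.5 | 0.7 |
|---|---|---|---|---|
| 12 superiority tests, either direction | 46.0% | 39.6% | 32.1% | 23.2% |
| 12 superiority tests, favouring ceftriaxone | 26.2% | 20.1% | 16.0% | 11.6% |
| Non-inferiority, any of 4 | 9.6% | 8.6% | 7.8% | 6.6% |
| Non-inferiority, any of 5 | 11.9% | 10.5% | 9.1% | 7.5% |

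The superiority rows assume no true difference on any outcome and take that step as reached. The non-inferiority rows assume a true deficit exactly at the margin on every outcome.

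**5. If all four primaries had to succeed.** Alpha would be held at 2.5%, and the price is power. With 230 / 2 = 115 per arm, power per endpoint is Φ(gap / SE − 1.96), where the gap is the distance from the true difference to the margin.

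- 85% in both arms: SE = √(2 × 0.85 × 0.15 / 115) = 0.0471, and Φ(0.10 / 0.0471 − 1.96) = 56.5%. All four: 0.565⁴ = 10% if independent, 26% at correlation 0.5, 33% at 0.7.
- 82% (ACPG) and 88% (ceftriaxone), the rates cited under Sample size: SE = √((0.82 × 0.18 + 0.88 × 0.12) / 115) = 0.0469, and Φ(0.16 / 0.0469 − 1.96) = 92.6%. All four: 0.926⁴ = about 74% if independent.

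Both cases apply serological rates to all four primaries, which is itself an assumption.

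**The case against.** The best defence is that overall response is the lead endpoint. The primaries are only additionally evaluated on their own, the missing-data sentence speaks of the primary outcome in the singular, and time to recovery is defined through overall response. Weights, a score cut-off and a testing order are commonly left to a full protocol or analysis plan that is not shown.

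Much of this is fair. The composite-first reading is plausible, and the absence of weights or a cut-off from an article is no finding. But the margin is not tied to the composite, and the sample size rests on serological cure instead. Nor is the superiority step left open: the article fixes 0.05 for every outcome, so a later plan that adjusted would depart from it.

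A reader might infer more than the text supports:

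- **That the abstract contradicts the body on the number of primaries.** It says "The primary outcomes will include cerebrospinal fluid (CSF) white blood cell (WBC) count, serological efficacy, and clinical efficacy". Serological efficacy can cover both CSF and serum RPR, so this is condensation.
- **That the plan refutes its own premise because** "The correlation between serum and CSF RPR titers will be analyzed". Examining a correlation of titers does not contradict assuming that none is obvious among response outcomes. At most it treats as open what the weighting takes as settled.
- **That serum RPR cannot carry the claim because both arms receive the same benzathine penicillin course.** Nothing in the document says this affects serum RPR more than the other outcomes.
- **That 13 superiority tests are planned (48.7%).** Overall response has no heading of its own among the outcomes; the listed family is 12.
- **That independence is the realistic case.** Nonresponse and recurrence reuse symptoms, CSF titer and CSF-WBC count, and time to recovery reuses the composite. The independence figures are upper ends.

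**Conclusion.** The point holds. The non-inferiority conclusion is not uniquely defined, and the superiority step, followed as written, leaves the confirmatory error rate uncontrolled.

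The superiority inflation follows from the stated rule. Its size (23–46% in either direction, 12–26% favouring ceftriaxone) depends on the unknown correlation, and every value in that range exceeds the nominal level.

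The non-inferiority inflation (7–12%) is conditional. It arises only if success on any one outcome is enough, and the document states no such rule, so it should not be read as the trial's actual error rate. Nor does the document support saying that power must collapse under an all-must-pass rule: independent endpoints give 10% at 85% in both arms and about 74% at the cited 82% and 88%.

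**What to change.** Before any outcome data are seen, state one of the following in the protocol, the analysis plan and the registry entry:

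1. **Overall response carries the 10-point test**, with expert weights and responder cut-off locked.
2. **CSF serological response carries it.** This is closest to the sizing basis, though not identical: the risk ratio cited there is for CSF-VDRL, while the outcome is CSF RPR within 1 year. A rule is needed for patients whose CSF RPR is nonreactive at baseline. The inclusion criteria can admit them on FTA-ABS or TPPA, and they cannot show a two-dilution fall or a reversion.
3. **All four primaries must meet the margin.**

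Which to choose is the sponsor's decision; each removes the ambiguity. After non-inferiority, superiority should be confirmatory only on the named endpoint, or on the four primaries with Holm correction under option 3. All other primary and secondary outcomes should be reported as estimates with 95% CIs or with Holm correction.

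The cost is wording, plus the loss of unadjusted formal superiority claims on the other outcomes. Recruitment began on 1 December 2021, so the amendment should be dated and should state what had been seen. Naming an endpoint does not by itself size the trial on the margin; power under the chosen rule should be stated with its assumed rates.

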This trial will meet high methodological standards, such as strict inclusion and exclusion criteria, adequate randomization and concealment of allocation, a PROBE design, the inclusion of independent statisticians, and multilevel quality control. These factors increase the credibility of the clinical trial results. Second, comprehensive outcomes will be evaluated to compare the efficacy of ACPG and ceftriaxone. Previous clinical trials have evaluated the efficacy of treatment for neurosyphilis based on rates of serological cure, clinical cure, and normalization of CSF-WBC counts and on protein concentrations [17, 27–30]. Several studies have also evaluated the use of neuroimaging examinations to determine the efficacy of neurosyphilis treatments [21, 31]. The present trial will also evaluate clinical improvements (including MMSE scores), adverse events, time to recovery, and recurrence of neurosyphilis. Evaluation of improvements in clinical manifestations will include improvements of the most common clinical manifestations of each clinical subtype of neurosyphilis during follow-up. These parameters have not yet been evaluated in previous studies and may provide strong evidence to determine the efficacy of treatment. Adverse events will be assessed to determine the safety of ceftriaxone. Disease recurrence, time to recovery, and 1-year follow-up results in patients with neurosyphilis may provide evidence for evaluating the long-term efficacy of the two drugs. In addition, because neurosyphilis patients are frequently lost to follow-up, the sample size calculated using a standardized formula has been increased to improve the reliability of outcomes. Finally, analysis of clinical factors, such as smoking, alcoholism, stage of disease (early or late neurosyphilis), asymptomatic or symptomatic status, baseline serum and CSF RPR titer [32], and CSF-WBC counts and protein concentration, may enable the identification of the factors related to treatment efficacy and obtain evidence for providing a more personalized and accurate treatment regimen.

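### The factor analysis is a screened main-effects model: it can show prognosis, but not which patients do better on which drug, so it does not support the personalised-regimen statement in the Discussion

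*Protocol article*

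**What the plan says.** The protocol article, under Statistical analysis, sets a two-step procedure. Step one: "Univariate analyses will be performed to identify potential factors associated with the treatment outcome, with variables having a *P* value ≤0.10 in univariate analyses" carried forward. Step two: the variables so selected go into a multivariable logistic model. Crude and adjusted odds ratios with 95% confidence intervals follow, and the section's general rule is that a two-sided P value "<0.05 will be considered statistically significant". No treatment-by-factor term is named. Nothing says that arm is kept in the model whatever its P value, and nothing labels the analysis exploratory.

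The Discussion gives the candidate factors as examples: "smoking, alcoholism, stage of disease (early or late neurosyphilis), asymptomatic or symptomatic status, baseline serum and CSF RPR titer", followed by CSF white cell count and CSF protein. It says their analysis "may enable the identification of the factors related to treatment efficacy and obtain evidence for providing a more personalized and accurate treatment regimen".

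**The concern.** Fitting the regimen to the patient requires evidence that the difference between regimens changes with a patient characteristic. A main effect does not give that. If late-stage patients respond less often, the model will report it even if they respond equally poorly on both drugs. Such a finding could then be presented as a reason to choose one drug, although no differential effect was tested.

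The second problem is selection. The same data choose the factors and supply the final P values and intervals, with no adjustment for the number of candidates. Those P values and intervals are therefore optimistic, and a factor that is pure noise has a fair chance of being reported.

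**Working it through.** **Method against use.** The procedure tests whether response varies with a factor in the two arms pooled. The Discussion's use needs a test of whether the arm difference varies with the factor. With arm A, factor F and logit link, the first concerns the coefficient of F and the second the coefficient of A×F. The first can be large while the second is zero. The stated model has no A×F term.

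**Is arm in the model at all?** The text does not say. Suppose arm were screened like any other variable. With the response rates cited under Sample size (82% and 88%), the unpooled z is 0.06 / √[(0.82×0.18 + 0.88×0.12)/n] with n per arm:
- n = 115: 0.06 / √(0.2532/115) = 1.28, P ≈ 0.20
- n = 145: 0.06 / √(0.2532/145) = 1.44, P ≈ 0.15

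At those rates the expected result misses the 0.10 threshold, so the final model could leave treatment out.

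**The plan's own numbers.** 7.85 × (2.5/0.5)² = 196.25, stated as 196. Then 196/0.85 = 230.6, stated as 230, and 230/0.80 = 287.5, stated as 290 (5 × 58). These reproduce apart from small rounding. The plan gives no error rate for the factor analysis, so the figures below are calculated for this review.

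**Number of candidates.** Eight are named: smoking, alcoholism, stage, symptomatic status, serum RPR, CSF RPR, CSF white cells and CSF protein. They are examples, so the list may be longer.

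**Chance of at least one false factor, one outcome, all eight null.**
- Eight independent tests at 0.05: 1 − 0.95⁸ = 33.7%.
- At least one passing the 0.10 screen: 1 − 0.90⁸ = 57.0%; expected number passing, 8 × 0.10 = 0.8.
- The two-step rule was simulated (3,000 trials per setting, 85% response, four binary and four continuous factors):

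| Patients | Pairwise correlation | At least one final false factor |
|---|---|---|
| 230 | 0 | 33.1% (a second simulation: 32.6%) |
| 230 | 0.3 | 22.9% |
| 230 | 0.5 | 15.6% |
| 290 | 0 | 32.0% |
| 290 | 0.5 | 14.9% |

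With independent factors the two-step rule does about as badly as eight unadjusted tests, so the screen gives no real protection. The selection effect shows in another ratio. In the second independent-factor simulation, 55.8% of trials had a null factor pass the screen and 32.6% ended with one significant: 0.326/0.558 = 58%. Once a null factor has passed the screen, the final 0.05 no longer means 5%.

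**Information available.** At 85% response, 230 × 0.15 = 34.5 non-responders, or 34.5/8 = 4.3 per candidate. At 88% and 82% response the counts are 27.6 and 41.4, or 3.45 and 5.2 per candidate. With all 290 patients, 290 × 0.15 = 43.5, or 5.4 per candidate.

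**Power for an interaction.** Assume 230 patients, a factor split evenly (57.5 per cell), 85% average response, and an arm difference that reverses sign between factor levels. The power of a two-sided 0.05 test on the logit scale is:
- ±5 points: 18%
- ±7.5 points: 35%
- ±10 points: 55%

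**The case against.** The strongest reply is that the Methods state a prognostic aim, which a main-effects model suits. The Discussion's sentence is hedged and never says the factors will be used to choose between the two drugs. Interaction terms, an exploratory label and a final covariate list are also commonly left to an analysis plan, which is not shown.

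Much of this stands. A reader might infer that the article promises personalised treatment; it says only that the analysis may help. The absence of interaction terms alone would be no finding. What remains is that the article itself fixes the threshold, the model and the significance level, and then states a use that this method cannot serve. An unseen plan could add terms, but these two sections would still disagree.

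The size also has limits:
- A reader might conclude that false factors are likely. The 15–33% range does not support that for one outcome: even under a full null, the more probable result is none.
- The all-null assumption is severe. Response is defined partly by falls in RPR titre and CSF white cell count, so their baseline values may well be related to it.
- Serum and CSF RPR may be correlated, which favours the lower part of the range.
- One might multiply the risk over the four primary outcomes and the overall response. The section refers to the treatment outcome in the singular and does not say the screen is repeated.
- The per-candidate counts describe the candidate list. Only variables that pass the screen enter the fitted model.

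**Conclusion.** The concern holds in limited form. The stated procedure can identify prognostic factors. It cannot show for whom ceftriaxone differs from penicillin G, so it does not support the personalised-regimen statement. That conclusion follows from the form of the model and needs no numerical assumption.

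The 15–33% figure rests on eight null factors, one outcome, 85% response, 230–290 patients and pairwise correlation from 0.5 down to 0. The count of about 35 non-responders applies the plan's 85% rate, which is based on serological response, to an outcome whose overall rate the article does not give.

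A reader might also infer that the main result is at risk. It is not: this is a secondary analysis, separate from the non-inferiority comparison and from the sample size. The severity is minor.

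**What to change.** Under Statistical analysis:
- Replace the P≤0.10 screen with a short list of baseline factors fixed in advance, for example stage, symptomatic status and baseline CSF RPR.
- Keep treatment arm in the model regardless of its P value.
- Label the model prognostic and exploratory.
- If anything is to be said about choosing between regimens, fit one model per listed factor with arm, factor and their interaction. Report the arm difference with its 95% confidence interval within factor levels, together with the interaction P value, all as exploratory.

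If the interactions are not added, limit the Discussion sentence to identifying prognostic factors.

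The cost is some rewording and a few models on data already collected. The drawback is the low interaction power shown above. A null interaction would not show that the drugs perform alike in all patients, so the claim becomes more modest either way.

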## Methods

### Study design

This prospective, multicenter, non-inferiority, randomized, controlled trial was designed to compare the efficacy of ACPG and ceftriaxone in the treatment of patients with neurosyphilis. Patients will be randomized 1:1 to treatment with ACPG or ceftriaxone. Clinical data will be recorded prior to treatment and 3, 6, 9, and 12 months after treatment. The flow diagram of this trial is shown in Fig. 1 and its schedule is shown in Fig. 2. This trial was designed in accordance with the World Health Organization (WHO) Trial Registration Data Set (TRDS) and all relevant items are present in this protocol.

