### Outcomes

All parameters will be assessed at baseline before treatment (T0) and at follow-up timepoints 3 (T1), 6 (T2), 9 (T3), and 12 (T4) months later.

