#### Secondary outcomes

##### MMSE score

General paresis is the most frequently reported clinical presentation of neurosyphilis in China [17], with patients having different levels of cognitive impairment. The Mini-Mental State Examination (MMSE), one of the earliest and most widely used brief cognitive assessment tools [18], is utilized to evaluate the severity of dementia among patients with general paresis [19]. In this study, MMSE scores will be determined before treatment and at each follow-up to determine the degree of recovery from cognitive impairment among patients presenting with general paresis at baseline.

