### Randomization

Block randomization will be used in the trial. Patients newly diagnosed with neurosyphilis will be randomly assigned 1:1 to the ACPG or ceftriaxone group. The randomization codes will be produced by an independent statistician at the head research center who was unaffiliated with this trial using PROC PLAN through SAS 9.2 software. Each sub-center will be assigned 58 block sequences, and the randomization schedule will be managed by independent investigators not involved in the implementation or statistical analysis of this study.

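### The stated arm comparisons use neither the centre-wise blocking nor the baseline values, which costs a little precision on the non-inferiority test and probably more on continuous outcomes

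*Protocol article*

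**What the plan says.** **Design.** The Randomization section says "Block randomization will be used in the trial" and "Each sub-center will be assigned 58 block sequences"; the Sample size section plans 58 patients per centre at five centres. The word stratified is not used, but blocking within centre is the natural reading.

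**Baseline data.** The Outcomes section has every parameter measured at T0. For patients presenting with general paresis, "MMSE scores will be determined before treatment and at each follow-up". The Discussion names candidate prognostic factors in advance, among them "stage of disease (early or late neurosyphilis), asymptomatic or symptomatic status, baseline serum and CSF RPR titer".

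**Analysis.** In Statistical analysis, "Normally distributed continuous variables in the two groups will be compared by" t tests, categorical variables by χ² or Fisher's exact test, and nonparametric variables by rank-sum tests. RPR titres are log2-transformed. No test has a centre term or a baseline covariate. The non-inferiority margin is an absolute difference of 10 percentage points.

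Separately, a search for factors associated with treatment outcome screens variables one at a time; those with P≤0.10 are "in univariate analyses included in a multivariate logistic regression model", which reports ORs and adjusted ORs.

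**The concern.** When allocation is balanced within centres and centres differ in success rate, an analysis that ignores centre gives standard errors that are somewhat too large. When the baseline value of an outcome predicts its later value, an analysis that ignores it, or only subtracts it, is less precise than one that adjusts for it. Both kinds of information are already collected here.

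The loss matters because precision is short for the margin if the two drugs are truly equal. In addition, the only adjusted result in the plan is an odds ratio, which cannot be set against a margin on the absolute scale.

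**Working it through.** **1. The plan's own figure.** With R = 1.5, (1+R)²/(1−R)² = 6.25/0.25 = 25, and 25 × 7.85 = 196.25, against 196 events stated. Then 196/0.85 = 230.6 (230 stated), and 230/0.8 = 287.5 (290 stated, which is 5 × 58). The chain reproduces. It is a calculation for detecting a difference at RR 1.5 and does not use the 10-point margin.

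**2. Power for the margin, unadjusted.** Inputs: 85% success in both arms (the plan's expected rate), 115 evaluable per arm (230/2), margin 0.10, one-sided 0.025. The plan names no interval method, so the simple difference with unpooled variance is taken.
- SE = √(2 × 0.85 × 0.15/115) = √(2 × 0.1275/115) = 0.0471
- Power = Φ(0.10/0.0471 − 1.96) = Φ(0.164) = 56.5%
- With all 290 analysed (145 per arm): 66.4%
- At 88% on ceftriaxone against 82% on ACPG, the rates the plan cites: Φ(0.16/0.0469 − 1.96) = 92.6% at 115 per arm

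**3. Gain from centre alone.** The spread of centre rates is assumed.
- 75, 80, 85, 90, 95%: mean p(1−p) = (0.1875 + 0.16 + 0.1275 + 0.09 + 0.0475)/5 = 0.1225, which is 3.9% below 0.1275. Power = Φ(0.10/√(2 × 0.1225/115) − 1.96) = 58.2%
- 80, 82.5, 85, 87.5, 90%: mean p(1−p) = 0.12625, a 1.0% reduction. Power = 56.9%

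**4. Gain from centre plus baseline covariates.** Multiply the variance by (1−R²), with R² assumed.

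| R² | Power, 115 per arm | Power, 145 per arm |
|---|---|---|
| 0 | 56.5% | 66.4% |
| 0.05 | 58.7% | 68.7% |
| 0.10 | 61.0% | 71.0% |
| 0.20 | 66.1% | 76.0% |

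Unadjusted, 80% power needs 2 × 0.1275 × 7.85/0.10² = 200.2, so 201 per arm. Adjustment alone would have to reach R² = 1 − 115/200.2 = 0.43, or 1 − 145/200.2 = 0.28 with no losses.

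A simulation (3000 runs per setting, five centres of 46, 85% response in both arms, linear adjustment for centre and one covariate with robust SE) agrees. Variance fell by about 2–3%, 9–10% and 17% for covariate effects of 0.5, 1.0 and 1.5 log-odds per SD. Power rose by about 1, 3–4 and 7–8 points. With no prognostic effect, variance was about 1% higher.

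**5. Continuous outcomes (MMSE, log2 RPR titres, CSF protein where analysed as values).** Let σ² be the variance at each visit and r the baseline–follow-up correlation (assumed). The variance is σ² for follow-up values, 2σ²(1−r) for changes and σ²(1−r²) for ANCOVA. The ANCOVA reduction is therefore r² against follow-up values and 1 − (1+r)/2 = (1−r)/2 against changes.

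| r | Against follow-up values | Against change scores |
|---|---|---|
| 0.5 | 25% | 25% |
| 0.7 | 49% | 15% |

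**The case against.** **The P≤0.10 screen is a different analysis.** A reader might infer that the arms are compared with covariates chosen by that screen, so that the treatment effect depends on chance selection and its interval is too narrow. The text does not support this. Statistical analysis presents the screen as a search for factors associated with outcome, and the Discussion gives the same purpose. All that remains is that nothing rules out quoting an adjusted OR for treatment as an efficacy result.

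**Baseline is not wholly ignored.** A reader might also infer that raw follow-up values are tested. The plan does not say whether values or changes are tested, and several response definitions are relative to baseline: the two-dilution RPR fall, the reductions in CSF-WBC and protein, and the symptom categories. HIV status is also used, since it sets the CSF-WBC threshold. This objection stands, and is why both ANCOVA comparisons are shown.

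**The gain on the decision is small.** This also stands. Centre alone is worth about 1–2 power points under a wide assumed spread. The larger percentages belong to continuous outcomes, and MMSE is secondary and limited to general paresis.

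**Covariates are often left to the SAP.** True, and their absence alone would be no finding. But the article does name the tests for the arm comparison, and the point concerns those stated methods.

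**Conclusion.** The point holds as one of efficiency, not validity. The named tests are sound; ignoring centre errs towards wider intervals. On the non-inferiority comparison the likely gain runs from about 0.4 to 1.7 power points for centre alone (assumed spreads of 80–90% and 75–95%) to about 4.5 points at an assumed R² of 0.10. There is none if centre and baseline do not predict response. The gain is probably larger for continuous outcomes, but its size depends on correlations that the document does not give.

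A reader might take better adjustment as a remedy for low power. It is not: the shortfall at equal true rates comes from sizing on RR 1.5, and R² would need to be about 0.28 to 0.43 to remove it. At the cited 88% against 82%, power is not short. The change is still worth making, because it is nearly free and matches the analysis to the randomisation.

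**What to change.** 1. Make the primary comparison a Mantel–Haenszel risk difference stratified by centre, with its 95% CI set against the 10-point margin. Compute it within each imputed data set and pool, since the plan imputes missing primary outcomes.
2. Analyse MMSE, log2 RPR titres and CSF protein values by ANCOVA or a mixed model with the baseline value and centre.
3. If a supportive adjusted analysis of the binary outcome is wanted, use a standardised risk difference with covariates fixed in advance. Keep them few: 15% of 230 is about 35 expected failures, and treatment plus four centre terms already use five parameters. State how a nonreactive CSF RPR is coded, since the entry criteria also accept other reactive CSF tests, and the log2 of a nonreactive titre is undefined.
4. State that the P≤0.10 screen and its adjusted ORs serve only the prognostic-factor analysis and are not used as an estimate of treatment effect.

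The cost is analysis wording, fixed before outcomes are seen by arm, and a little extra programming. No new data are needed. The downside is that nothing is gained if centre and baseline turn out not to predict outcome.
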